**Figure 1 fig1:**
[figure not shown]
Flow diagram for study design. Study phases and outcome measures.

### Statistical analyses

3.6

The data will be processed primarily using the statistical software IBM SPSS Statistics 29, among others, and mainly the following analyses will be performed:

First, descriptive analyses will be carried out for all variables to identify possible errors or outliers in dataset. Then, zero order correlation analyses will be computed to determine the degree of association between variables; and partial correlation analyses will be conducted to examine its association excluding the effect of other confounding variables.

Additionally, as main statistical analysis, a mixed Analysis of Covariance will be performed to evaluate the main effects between groups (2 types of transplant: solid organ and haematopoietic) and within groups (time variable with 3 levels: pre-, post-transplantation at 4-weeks and 6-months follow-up) as well as potential interactive effects, excluding the effect of confounding variables. *P*-value adjustments for multiple comparison will be performed. In turn, other analytical strategies will be used to examine time series such as latent grow models. Finally, innovative statistical analyses based on multiple linear regression will be developed to examine the relative weight of the different predictor variables on the criterion variables, already published elsewhere (Fernández-Jiménez and Arnett, 2015).

All these statistical analyses will be complemented with the appropriate effect size indexes for each statistical test (e.g., *f*, omega-square and *R^2^* indexes) (Cohen, 1992). Additionally, Reliable Change Index (RCI) will be computed in order to determine the real change of each individual score between measurements over time (Kiselica et al., 2023).

Since the main statistical analysis in this study will be a mixed Analysis of Covariance (2 × 3), with a statistical power = 0.95 and a risk/significance level of alpha = 0.05, to detect at least a moderate effect size (*f* = 0.25) on the outcome variables included, a minimum sample size of 36 patients will be required according to GPower 3.1.9.4 software.

Regarding the qualitative study of this project (focus groups), thematic analysis techniques will be used, following the Clarke and Braun’s procedures (Clarke and Braun, 2021), in order to synthesize the themes (major and minor) related to the unmet care needs during the transplantation process. Themes will be derived from the data and not identified in advance. Two data coders will independently code the transcripts. Any disagreement will be resolved by consensus.

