### Hypotheses

2.1

The hypotheses of the present study are listed below and are based on clinical experience as well as on the available scientific literature (Caes et al., 2021):

*H1:* Improvements in some neuropsychological domains (e.g., processing speed and executive functioning) will be observed between the pre- and post-transplant phases.

*H2:* Improvement in some parent- (or guardians-) and patient-reported outcomes (e.g., emotional-behavioral problems and personal adjustment) will be observed between the pre- and post-transplant phases.

*H3:* Patients under cardiac and lung transplantation will suffer poorer neuropsychological outcomes and more emotional-behavioral problems, both in the pre- and post-transplantation phase, than patients under kidney transplantation.

*H4:* Patients under hematopoietic transplantation will suffer poorer neuropsychological and more emotional-behavioral problems, both in the pre- and post-transplantation phase, than patients under solid organ transplantation.

*H5:* Older patients will show poorer therapeutic adherence levels than younger patients.

*H6:* Executive functioning will mediate the relationship between several patient-reported outcomes (e.g., pain, anxiety, depression and sleep disorders) and therapeutic adherence.

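### The stated 0.95 power at 36 patients fits the time and group-by-time effects, not the solid organ versus haematopoietic main effect behind H4, which has power of about 0.60 to 0.65 even at the planned 60

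*Protocol article*

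**What the plan says.** Under Statistical analyses (3.6), the protocol article states that "a mixed Analysis of Covariance will be performed to evaluate the main effects between groups (2 types of transplant: solid organ and haematopoietic"). The model also has a factor for visits, described as a "time variable with 3 levels: pre-, post-transplantation at 4-weeks and 6-months follow-up"; the possible interaction of the two is to be tested too. Confounders are to be adjusted for.

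The last paragraph of 3.6 sizes the study on this 2 × 3 model. The error rates are given as follows: "with a statistical power = 0.95 and a risk/significance level of alpha = 0.05". The target is put this way: "to detect at least a moderate effect size (*f* = 0.25) on the outcome variables included". The paragraph then concludes: "a minimum sample size of 36 patients will be required according to GPower 3.1.9.4 software". It does not say which of the three effects the figure refers to, and it gives no correlation between visits.

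Under Hypotheses (2.1), H4 reads: "Patients under hematopoietic transplantation will suffer poorer neuropsychological and more emotional-behavioral problems, both in the pre- and post-transplantation phase". The comparator is the solid organ patients, so this is the two-level group factor of the model, taken across visits. Under Selection of participants (3.2), the planned sample is 60.

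**The concern.** A mixed model with three visits has very different power for its different effects. When visits within a patient are positively correlated, tests of change over time gain, because each patient serves as his or her own control. Tests of the difference between groups lose, because repeated visits then add little independent information about the patient's average level. One sample size therefore cannot give the same power for both kinds of test, except by coincidence.

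Because 3.6 lists the group effect first and then gives a single figure for the whole model, a reader will take H4 to be tested with 95% power. If the group effect is then not significant, it may be taken as good evidence that haematopoietic and solid organ patients do not differ. Comparison by type of transplant is a stated objective (section 2), so this would bear on one of the study's main messages.

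**Working it through.** **Inputs from the document (3.6, 3.2):** k = 2 groups ("2 types of transplant: solid organ and haematopoietic"), m = 3 visits, f = 0.25, alpha = 0.05, target power 0.95, stated minimum N = 36, planned N = 60.

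**Assumptions (not in the document):** correlation between visits r, shown over 0 to 0.9 with 0.5 and 0.6 highlighted; sphericity; complete data; equal groups unless stated; no gain from covariates.

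**Formulas** (noncentral F, in the G*Power parameterisation for repeated measures):
- Time and group-by-time: λ = f²·N·m/(1 − r), df1 = m − 1 (for the interaction (k − 1)(m − 1), the same value here), df2 = (N − k)(m − 1).
- Group main effect: λ = f²·N·m/(1 + (m − 1)r), df1 = k − 1, df2 = N − k.
- Unequal groups: multiply the group-effect λ by 4p(1 − p), where p is the share in the smaller group.

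**Step 1. Reproduce 36.** For the time or interaction test at N = 36 and r = 0.6, λ = 0.0625 × 36 × 3/0.4 = 16.875 with df 2 and 68, and power is 0.958. In steps of two (equal groups), 36 is the smallest N that reaches 0.95. So the stated figure is obtainable for these two tests. At r = 0.5, λ = 13.5 and power at 36 is 0.906.

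**Step 2. The same N for the group effect.** At N = 36 and r = 0.6, λ = 0.0625 × 36 × 3/2.2 = 3.07 with df 1 and 34, and power is 0.398. At N = 60, λ = 0.0625 × 60 × 3/2.2 = 5.11 with df 1 and 58, and power is 0.604.

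| r | Group effect, N = 36 | Group effect, N = 60 |
|---|---|---|
| 0 | 0.71 | 0.91 |
| 0.5 | 0.43 | 0.65 |
| 0.6 | 0.40 | 0.60 |
| 0.9 | 0.33 | 0.50 |

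Even at r = 0, the most favourable non-negative value, the group effect does not reach 0.95 at 36 or at 60. The N needed for 0.95 is 72 at r = 0, 142 at r = 0.5 and 156 at r = 0.6.

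**Step 3. Unequal groups.** The document gives no split. As an illustration, with one quarter of patients in the smaller group, 4 × 0.25 × 0.75 = 0.75. At r = 0.6 power falls to 0.31 at N = 36 and 0.49 at N = 60.

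**Step 4. What 60 patients can detect.** With equal groups, r = 0.6 and no covariate gain, the f that gives 0.95 power for the group effect at N = 60 is about 0.41, against the 0.25 stated.

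**Step 5. Time and interaction at 60.** Power is 0.953 at r = 0.3, 0.976 at r = 0.4 and 0.991 at r = 0.5. For these effects the planned sample delivers the stated power from r of about 0.3 upwards, given sphericity and complete data.

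**The case against.** Four points on the other side deserve weight.

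- **The plan is for 60 patients, and 36 is only a minimum.** This is right, and it changes the size of the problem. A reader might infer that the planned study has power of about 0.40 for H4, or that it would miss a moderate difference more often than find it. The first describes 36 patients. The second does not hold at 60 with equal groups, where power is 0.60 to 0.65. But 0.60 to 0.65 is still not 0.95.
- **The model is an ANCOVA.** Covariates that explain outcome variance would raise power. With an assumed covariate R² of 0.3 or 0.5 (λ divided by 1 − R²), the group effect at N = 60 and r = 0.6 would have power of about 0.76 or 0.88. The document gives no R², so the stated 0.95 cannot rest on this, but the unadjusted figures are one scenario and should be labelled so.
- **The correlation may be in the full protocol.** An article commonly leaves such an input out. A reader might infer that 36 is a mistake, since r = 0.5 gives 44 for the time and interaction effects, and four visits at r = 0.5 also give 36. The document does not support that: 36 follows from the stated design at r of about 0.6, its origin cannot be established, and at 60 patients the difference has no consequence. The unstated correlation is not the error.
- **The limits are conceded in the Discussion.** They are conceded only for comparisons between types of solid organ. A reader might extend the present point to H3 (cardiac and lung versus kidney). H3 is a contrast within the solid organ patients, not the two-level factor of this model, so the figures here are not its power, and its limit is already acknowledged. Nothing comparable is said about solid organ versus haematopoietic.

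It is also fair that the plan promises effect sizes for every test and nowhere says that a null group effect will be read as no difference. That makes the harm a risk of misreading, not a declared intention.

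**Conclusion.** The point stands for H4. Section 3.6 attaches one power figure to a model that expressly includes the transplant-type main effect, and the design does not deliver that power for this effect. With equal groups, f = 0.25, alpha 0.05 and no covariate gain, power is about 0.40 to 0.43 at 36 patients (0.33 to 0.71 over correlations of 0.9 to 0). At the planned 60 it is about 0.60 to 0.65 (0.50 to 0.91 over the same correlations). The exact values depend on the unstated correlation, group split and covariates. The conclusion that 0.95 is not reached holds for every non-negative correlation at either size, unless covariates explain enough variance, which the document does not quantify. The time and group-by-time effects, which serve the change-over-time hypotheses H1 and H2, are not in question at 60 patients with r of about 0.3 or more.

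**What to change.** In the last paragraph of 3.6:

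1. State that 36 patients at 0.95 power and f = 0.25 refers to the time and group-by-time effects only, and name the correlation between visits that was assumed (about 0.6 reproduces it), with sphericity and complete data.
2. Report the power of the solid organ versus haematopoietic main effect separately at the planned 60: about 0.60 to 0.65 at f = 0.25 for correlations of 0.6 to 0.5, and a detectable f of about 0.41 for 0.95 power at a correlation of 0.6. Label these as equal groups and unadjusted, and say that an unequal split lowers them.
3. Present H4 as an estimated difference with a confidence interval, and state that a non-significant group effect will not be read as absence of a difference.

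This is a change of wording only and needs no extra patients. The cost is that the published power statement becomes less favourable for H4.

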## Discussion

4

This study aims to examine neuropsychological functioning and other biopsychosocial outcomes, therapeutic adherence and unmet care needs in paediatric population undergoing solid organ or allogeneic hematopoietic transplantations during the pre- and post-transplantation phases. The scientific literature encourages the incorporation of specific measures for mental health concerns as these can impact quality of life, morbidity and mortality in this population (Penner et al., 2022). Moreover, studies have confirmed that this clinical population presents outstanding needs related to impairment in specific neurocognitive domains. Therefore, given the wide range of neurocognitive deficits that have been identified in the paediatric population exposed both to solid organ transplantation and hematopoietic transplantation, this project has designed a comprehensive assessment protocol, covering the most common potential neuropsychological problems in this clinical population, such as intelligence, processing speed and attention, verbal and visual memory, and executive functioning measures (Reed-Knight et al., 2015; Buchbinder et al., 2018).

This project aims to fill the gap in the scientific literature regarding the comparison in patients’ neurocognitive performance and biopsychosocial domains before and after a transplantation process in order to assess change, prevent negative outcomes, and/or orientate adequate interventions.

Also, the results and conclusions derived from this project will be directly transferred to routine clinical practice and real-world patients. As mentioned above, the use of standardized measures (neuropsychological tests and biopsychosocial questionnaires) by the Mental Health team during the entire transplantation process will allow the early detection of potential neuro−/psychosocial problems, as well as the implementation or prescription of the adequate specific intervention (therapeutic or preventive) that may be required at an early stage (Karakizlis et al., 2022). For example, family disfunctions can be identified during any stage of the transplantation process so that an early intervention can be applied by Mental Health professionals (Cushman et al., 2019; Liu et al., 2020; Tadros et al., 2020). Consequently, this is expected to have a positive impact on the prognosis of the neurocognitive and mental health problems detected.

In short, the results of the pre- and post-transplant biopsychosocial and neuropsychological assessments will help to guide future clinical or educational interventions, if necessary, as well as to plan other activities to strengthen the patient’s resources, always with the aim of improving their personal, family, social and school adaptation. In the event that parents/legal guardians so request, clinical reports will be issued with recommendations that will help the patient’s educational centres to guide potential adaptations (curricular, assessment, or methodological) according to pedagogical criteria.

Among the methodological strengths of this study is the multi-method/multi-source approach, which includes not only self-/parent-reported questionnaires, but also objective neuropsychological tests and blood levels of prescribed drugs, thus avoiding common method bias (Podsakoff et al., 2012). These measures will constitute a multidomain set of outcomes that includes variables relevant to transplant recipients, their caregivers, and health professionals for decision making (Annema et al., 2023). However, our study presents several limitations. First, we will use a non-random sampling technique that increases the probability of some degree of collider bias and limits the generalizability of the findings. Second, because of the observational nature of the design, sound causal inferences cannot be drawn. Third, given the modest number of patients from the paediatric population undergoing a transplantation process, intergroup comparisons between types of solid organ transplants will be limited. Fourth, due to the clinical setting in which this project is implemented, other neurocognitive domains focused more specifically on school performance, such as reading or writing, will not be addressed. Last, attrition during post-transplantation or follow-up phases could bias the results because patients suffering more severe medical complications could be excluded from assessments, during the prefixed measurement times in this study.

Finally, the protocolisation of the assessment and monitoring of these clinical populations aims to create a working dynamic, of greater coordination between departments in our hospital, that will last beyond the years of this project, increasing the awareness among other clinicians about the potential neurocognitive and psychological needs of the patients and their relatives during the transplantation process.

## Conclusion

5

A protocolised plan such as the one proposed in this project will allow the children hospital of La Paz University Hospital to improve the attention and care of all the participants in the transplant process: the patients, their families and the reference professionals.

Ultimately, this project aims to create a structured and permanent clinical care programme for children and adolescents undergoing transplantation, as other countries have been developing, given that the biopsychosocial repercussions suffered by these patients and their families continue for years after transplantation. Finally, the results will be disseminated in a clear and transparent manner, allowing for other healthcare centres to use them (Kikuchi and Kamibeppu, 2015; Bastos Tavares et al., 2022).

## Ethics statement

The standards of good clinical practice and the ethical principles for research involving human beings established in the Declaration of Helsinki and its subsequent revisions will be met at all times. This study was approved by the Research Ethics Committee of La Paz University Hospital (Madrid, Spain) (institutional code: PI-5223). Legal guardians of patients (or, when applicable, patients of legal age) will provide their written informed consent to participate in this study.
